# A multi-centre, randomized, controlled trial on coaching and telemonitoring in patients with cystic fibrosis: conneCT CF

**DOI:** 10.1186/s12890-021-01500-y

**Published:** 2021-04-21

**Keywords:** Cystic fibrosis, Telemedicine, Adherence, Home spirometry

## Abstract

**Background:**

The extend of lung disease remains the most important prognostic factor for survival in patients with cystic fibrosis (CF), and lack of adherence is the main reason for treatment failure. Early detection of deterioration in lung function and optimising adherence are therefore crucial in CF care. We implement a randomized controlled trial to evaluate efficacy of telemonitoring of adherence, lung function, and health condition in combination with behavior change interventions using innovative digital technologies.

**Methods:**

This is a multi-centre, randomized, controlled, non-blinded trial aiming to include 402 patients ≥ 12 years-of-age with CF. A standard-of-care arm is compared to an arm receiving objective, continuous monitoring of adherence to inhalation therapies, weekly home spirometry using electronic devices with data transmission to patients and caring physicians combined with video-conferencing, a self-management app and professional telephone coaching. The duration of the intervention phase is 18 months. The primary endpoint is time to the first protocol-defined pulmonary exacerbation. Secondary outcome measures include number of and time between pulmonary exacerbations, adherence to inhalation therapy, changes in forced expiratory volume in 1 s from baseline, number of hospital admissions, and changes in health-related quality of life. CF-associated medical treatment and care, and health care related costs will be assessed by explorative analysis in both arms.

**Discussion:**

This study offers the opportunity to evaluate the effect of adherence interventions using telemedicine capable devices on adherence and lung health, possibly paving the way for implementation of telemedicine in routine care for patients with CF.

*Trial registration*: This study has been registered with the German Clinical Trials Register (Identifier: DRKS00024642, date of registration 01 Mar 2021, URL: https://www.drks.de/drks_web/navigate.do?navigationId=trial.HTML&TRIAL_ID=DRKS00024642).

**Supplementary Information:**

The online version contains supplementary material available at 10.1186/s12890-021-01500-y.

## Background

Cystic fibrosis (CF) is an inherited multi-organ disorder that causes damage mainly to the lungs, but also to organs of the digestive system such as the pancreas and liver (1, 2). CF is caused by mutations in the cystic fibrosis transmembrane conductance regulator (*CFTR*)-gene leading to abnormal function of the CFTR anion channel in the epithelium of different organs. The recent development of highly effective CFTR-directed therapeutics is currently transforming the care of patients with CF leading to an increase in lung function, an improvement in quality of life and a decrease in pulmonary exacerbations (3–5). However, the extent of the lung disease with lung function as a surrogate marker is the most important prognostic factor for survival (6, 7). Irreversible lung damage, e.g. bronchiectasis, has often already occurred in pediatric and adult patients by initiating of the new CFTR-directed therapies (8). Therefore, inhalation therapies with antibiotic and mucolytic agents remain a cornerstone of symptomatic therapy (1, 9, 10). These therapies are incredibly time-consuming and adult patients with CF usually spend at least 1.8 h per day performing an average of seven inhalations (11). In the face of this immense treatment burden, lack of treatment adherence was identified as the leading cause for treatment failure (12). Compared to electronic monitoring, which shows adherence to only 30–50% of all prescribed treatments, self- and clinician-reported adherence overestimate adherence substantially (11, 13–15). In the current standard of care, the CF physician has no objective information on the patient’s adherence, state of health and quality of life between the scheduled visits. Readily available information on adherence and lung function would allow for greater patient self-management of the disease and also for early intervention and adjustment of therapies by the CF physician, potentially preventing pulmonary exacerbations and slowing lung disease progression.

The role of digital technologies in supporting patients with CF in managing their complex therapies is being more and more acknowledged (16). Recently developed data-tracking nebulizers enabling patients to inhale all standard medications allow for accurate monitoring of inhalation therapies. Home monitoring strategies, including spirometry and symptom reporting, have been used for early detection of pulmonary exacerbations with conflicting results (17–20). Patients with CF are often cared for in specialized CF clinics. Regular follow-up visits delivered by trained, multidisciplinary teams have led to improvements in CF care and patient outcomes, but this centralization means longer travel distances for patients, resulting in more missed school and work. Especially in between routine visits, video-conferencing appears to be a promising option for delivering health care while reducing travel time, but has only been assessed in small studies (16).

This multi-centre trial aims to evaluate telemedicine’s effect including telemonitoring of inhalation therapy and lung function, a self-management app, video-conferencing and telephone coaching on adherence to treatment, lung function, and pulmonary exacerbations in patients with CF. The aforementioned digital technologies, combined with individualized phone coaching by psychologists as an intervention for behaviour change, are applied to achieve this goal. We hypothesize that this intervention leads to improved adherence, a prolonged time between pulmonary exacerbations, improved lung function and higher quality of life than patients receiving routine care.

## Methods/design

### General study protocol

This study is a randomized controlled, multi-centre, non-blinded trial in patients with CF. We present the second version of the study protocol issued 03 December 2020 following the first version issued 24 September 2020. First patient in was in March 2021 and recruitment continues until 30 September 2021. A standard-of-care arm is compared to an intervention arm using the following technologies: objective, continuous monitoring of adherence to inhalation therapies, weekly home spirometry using electronic devices with data transmission to patients and caring CF physicians combined with a self-management app, video-conferencing and professional telephone coaching (see Fig. 1). In standard-of-care, scheduled visits with the caring CF physician take place once quarterly. Further visits only occur at the patient’s request in cases where the patient’s health status deteriorates. In order to evaluate the study interventions in different medical settings, participants will be recruited at CF centres at four sites: (1) two major cities (Charité – Universitätsmedizin Berlin; Cystic Fibrosis Centre Munich-West), (2) one conurbation (University Medicine Essen), and (3) one rural area (University Medicine Rostock and three associated doctor’s practices). The Ethics committee of Charité – Universitätsmedizin Berlin, Germany, has approved the study (application number EA2/241/20) and the study was registered with the German Clinical Trials Register (Identifier: DRKS00024642). PARI Pharma Ltd. provides the eTrack Controller and the 2net Hub (Philips, North America). All study costs are covered by the German Innovation Fund with the funding number: 01NVF19008. The funders had no role in the design, management, analysis and reporting of the study.

**Fig. 1 Fig1:**
[figure not shown]
Standard of care for patients with CF compared to the intervention group in connect CF. A standard-of-care arm is compared to an intervention arm using objective, continuous monitoring of adherence to inhalation therapies, weekly home spirometry using electronic devices with data transmission to patients and caring physicians combined with a self-management app, video-conferencing and professional telephone coaching. In standard-of-care, scheduled visits with the caring CF physician take place once quarterly

### Study population

To be eligible for the study, participants must have a confirmed diagnosis of CF, be age 12 years or older and be able to give written informed consent or assent. In case of minor participants, the written informed consent of the legal guardian must also be provided. Study physicians obtain consent and assent. In addition, participants must have had at least one pulmonary exacerbation in the year before enrolment, a lung function with a forced expiratory volume in one second (FEV1) < 90% of the predicted value at the day of inclusion and if receiving a CFTR modulator therapy, participants must be stable on this treatment for the last three preceding months with no planned change in CFTR modulator treatment during the study period. A pulmonary exacerbation is defined according to the Bilton criteria (modified Fuchs criteria) as an episode of decreased pulmonary function caused by infection and treated with additional antibiotic therapy for at least two of the following reasons (21, 22): change in the amount of sputum or colour, increased cough, malaise, fatigue, lethargy, anorexia or weight loss, decrease in FEV1 by 10 percent or more from the last previously recorded values and/or radiographic changes indicative of pulmonary infection or increased dyspnoea.

Exclusion criteria include an acute depressive or psychotic episode, substantial immobility, no prescribed inhalation therapy, insufficient knowledge of the German language, lack of possession of a smartphone, being post-lung-transplantation, not being able to perform lung function testing, or lung function testing is contraindicated (e.g., because of pneumothorax or lung surgery within the previous three months). Participation in other intervention studies is also an exclusion criterion unless it is an open label study with the participation of already three or more months without planned cessation within our study duration.

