### Sample size calculation

Sample size calculation was performed by Private Institute for Applied Health Services Research (inav) GmbH and is based on the following assumptions: (1) primary endpoint: time to pulmonary exacerbation (30), (2) median time to exacerbation is 30% less in the CG compared to the IG based on estimation of involved CF experts, (3) event-free survival within 12 months in 25% of participants (18), (4) a significance level α = 0.05 and power of 1 – β = 0.8, (5) dropout rate of 20% (18) and (6) exponential distribution of survival and proportional hazards. Following these assumptions, a sample size of 391 participants is needed. To account for possible deviations from the assumed survival and dropout rate, we aim to recruit 402 patients. Participants are recruited as part of their routine visit at their CF centre by research personnel.

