Our study has some limitations: due to the study design’s nature, blinding of the patients and staff is not possible. Participation in this trial will be offered to all patients meeting the inclusion criteria. Nevertheless, only very motivated patients may agree to participate, leading to a selection bias. Additionally, a performance bias could occur because staff and patients of the participating centres might be more aware of the issue of adherence. This bias might lead to an increase in adherence also in the CG possibly diminishing our ability to detect differences in adherence between the IG and CG.

The coronavirus disease 2019 (COVID-19) pandemic has highlighted the importance and potential of digital technologies in patient care, and different strategies have been rapidly implemented (49–51). Scientific evidence for the feasibility, clinical benefit and cost-effectiveness of these interventions in patients with chronic conditions like CF is urgently needed to form the basis of a regulatory framework to authorize, integrate, and finance telemedicine services (52).

In summary, this study offers the opportunity to establish structures for secure data transmission, evaluate the use of telemedicine capable devices and adherence interventions on lung health and its cost-effectiveness, and possibly pave the way for implementation of telemedicine in routine care for patients with CF.

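### The open-label exception to the co-enrolment bar is not limited by type of intervention, so a control patient could stay in another telemonitoring, adherence or coaching study throughout follow-up

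*Protocol article*

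**What the plan says.** Under Study population, the protocol article bars co-enrolment with one exemption: "Participation in other intervention studies is also an exclusion criterion unless it is an open label study". The rest of the sentence sets two conditions. The patient has already taken part for at least three months, and no end to that participation is planned while this trial runs. The sentence does not restrict what the other study tests. None of the exclusions printed beside it concerns home spirometry, adherence tracking or coaching.

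The comparator is described in two places. The Background says that in current standard care "the CF physician has no objective information on the patient" between scheduled visits, with regard to adherence, state of health and quality of life. The General study protocol says that in standard care "scheduled visits with the caring CF physician take place once quarterly", with further visits only when a patient asks because of deterioration.

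Under Study flow and study intervention, CG patients receive a study nebulizer whose adherence data are hidden from patient and physician. Table 1 collects CF-associated medical treatment and care in both arms at t3, t4 and t5.

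**The concern.** A telemonitoring or coaching study can hardly be blinded; the Discussion says that blinding patients and staff is impossible in this one. Studies of the type most likely to overlap with the tested intervention are therefore open label, and the exemption lets them through. The condition that the other participation is not due to stop then means that a co-enrolled CG patient would have the outside intervention during the whole of follow-up.

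Such a patient would receive part of what the intervention group (IG) receives, and a co-enrolled IG patient would have less to gain. Randomisation should balance these patients between arms, so the risk is attenuation towards no effect and not confounding. What is at stake is how a null result on time to first exacerbation would be read. Without a record of outside use it would be hard to tell an ineffective package from a control arm that partly had it.

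**Working it through.** **1. Following the text.** Take a patient four months into an open-label study of adherence feedback and telephone coaching, with no planned end.
- The co-enrolment bar does not apply, because both conditions of the exemption are met.
- No other printed exclusion applies.
- Allocation is 1:1, so the patient may enter the CG.
- Hiding the study nebulizer's data blocks information from that device only. It does not block outside spirometry, coaching or video contact.

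The printed rule therefore admits a patient who does not fit the comparator of the Background and the General study protocol.

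**2. Reproducing the planned sample size.** Inputs from Sample size calculation:
- "a significance level α = 0.05 and power of 1 – β = 0.8". Sidedness is not stated; I assume two-sided.
- "median time to exacerbation is 30% less in the CG compared to the IG based on estimation of involved CF experts". With exponential survival this is a hazard ratio (HR) of 0.70, IG to CG.
- 25% event-free at 12 months (arm not stated), and 20% dropout.
- 18 months of follow-up, from the description of the intervention phase.

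Freedman events: (1.960 + 0.842)² × (1.7/0.3)² = 7.849 × 32.11 = 252.04, rounded up to 253. With the 25% read as the CG value, event-free survival at 18 months is 0.25^1.5 = 0.125 in the CG and 0.125^0.7 = 0.233 in the IG. The mean event probability is 1 − (0.125 + 0.233)/2 = 0.821. Then 253/0.821 = 308.2 and 308.2/0.8 = 385.3, so 386. Other readings give 393, 394 and 396. The stated 391 is within 3% of all of these. The sample size is not wrong on its own inputs; those inputs make no allowance for CG patients who already have intervention-like care.

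**3. Effect of such patients.** Let a share f already have the full benefit. Approximately, log HR = (1 − f) × ln 0.70, and power = Φ(|log HR| × √D/2 − 1.960). Schoenfeld's formula gives D = 4 × 7.849/(ln 0.70)² = 246.8, so 247 events.

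As a second check, log-rank power was simulated with 160 evaluable patients per arm (402 × 0.8/2 = 160.8), exponential times and censoring at 18 months, giving a fraction f of the CG the IG hazard. Two readings of the 25% were used: across both arms together (CG hazard 1.667 per year) and in the CG alone (1.386 per year).

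| f (assumed) | HR | Power, 247 events | Simulated, 25% overall | Simulated, 25% in CG |
|---|---|---|---|---|
| 0% | 0.700 | 80% | 84% | 82% |
| 5% | 0.713 | 76% | 80% | 78% |
| 10% | 0.725 | 71% | 75% | 74% |
| 20% | 0.752 | 61% | 64% | 61% |
| 30% | 0.779 | 50% | 53% | 51% |

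The simulations start above 80% because 18 months of follow-up in 320 evaluable patients yields more than 247 events; in the second reading, 320 × 0.821 = 263. The loss at f = 10% is 8.7 points by formula (80.0 − 71.3), 9.8 in the first simulation (84.5 − 74.7) and 8 in the second (82 − 74). If outside users have half the benefit, the loss is roughly half.

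**4. The recruitment margin.** 402/391 = 1.028. Required events grow as 1/(1 − f)², so this margin alone absorbs f = 1 − 1/√1.028 = 0.014, or 1.4%. The article assigns it to deviations in survival and dropout.

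**The case against.** The strongest reply is that nothing in the article shows one eligible patient with such exposure. No telehealth study is named as open to patients at these sites; the one ongoing telehealth trial whose location is given is in the United Kingdom. The exemption is built like the CFTR modulator criterion beside it (three months stable, no planned change), so the authors may have had long-running drug studies in mind. This stands as a limit on likelihood. It does not change what the sentence permits.

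A reader might infer from the Discussion's remark on the pandemic, that "different strategies have been rapidly implemented", that control patients were already using these tools. The document does not support that. The remark concerns patient care in general, and the next sentence calls evidence in conditions like CF still urgently needed.

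A reader might also infer that outside use would go unrecorded. That is not shown. Table 1's treatment-and-care item covers both arms at t3 to t5, and clinical history and therapy plan are taken from t0; the case report form itself is not available. What stands is narrower: the treatment-and-care item is absent at t0, and no row names outside spirometry, adherence apps, coaching or video consultations.

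The exclusion list is introduced as non-exhaustive in a condensed article, so the full protocol may add items. For that reason the point rests on the co-enrolment rule, which is printed as a complete sentence, and not on an absent exclusion.

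Finally, background digital care is part of standard care as delivered, and the trial deliberately recruits in different settings. This is a good argument against excluding all routine-care users, but not against narrowing the exemption.

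**Conclusion.** The point holds in limited form. As printed, the open-label exemption can place a patient with an ongoing telemonitoring, adherence or coaching intervention in the CG for all of follow-up, contrary to the stated comparator. The contrast could be attenuated; that it is attenuated would be a stronger claim, and the document gives no prevalence to support it.

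The sizes are illustrations. They assume a two-sided test, HR 0.70, 20% of patients contributing no data, and outside users with the full benefit of the package, which is severe because a single component is not the whole bundle. On those terms a 10% share costs roughly 8 to 10 points of power. A 5% share leaves 78 to 80% in the simulations, or 76% if exactly 247 events are observed. The planned sample size itself reproduces and is not in question.

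**What to change.** - State that the open-label exemption does not cover studies of telemonitoring, adherence or coaching interventions.
- Add one case report form item, in both arms at t0, t3, t4 and t5, for any home spirometry, adherence app or tracking, coaching or video consultation outside the trial.
- Report it by arm, with a sensitivity analysis of the primary endpoint leaving out patients with such use at t0. Use recorded at t0 precedes the intervention, so this restriction does not depend on events in follow-up. Later use should be described, not used to drop patients.
- Do not exclude routine-care users outright. That would narrow the pragmatic comparison and make a wider change to eligibility during recruitment.

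The cost is one amended sentence, one form item and possibly a few otherwise eligible patients. Recording remains useful even though enrolment has begun.

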### Randomization

A 1:1 randomization to the intervention group (IG) and control group (CG) is performed by an electronic-data-captures-system (EDC-Systems, secuTrial^®^) across the participating centres following study inclusion. Participants are stratified by age (12–17 years and ≥ 18 years of age), sex, CFTR modulator therapy, and lung function (FEV1 < 40% and FEV1 ≥ 40% predicted value at baseline/screening).

### Study flow and study intervention

Study flow and study intervention are depicted in Fig. 2 and an overview of applied survey instruments and collected data is provided in Table 1. During the preparation phase, which lasts up to six weeks, study procedures are explained to the participants, informed consent is obtained, and the participant is trained in the correct handling of the study devices.

**Fig. 2 Fig2:**
[figure not shown]
*Study phases and procedures.* During the preparation phase, participants are 1:1 randomized (R) to the intervention group (IG) and control group (CG), study procedures are explained and the correct handling of the study devices is being trained. The IG obtains a telemedicine capable nebulizer (eFlow rapid + nebulizer system, PARI Pharma GmbH, Germany), a home spirometry (mySpiroSense, PARI GmbH, Germany) and a CF therapy management app (PARI Connect App, PARI Pharma GmbH, Germany). The CG also receives a telemedicine capable nebulizer (eTrack Controller with eFlow rapid nebulizer, PARI Pharma Ltd, Germany, and 2net Hub, Philips, North America). During the phase of assessment of adherence, adherence to inhalation therapy is calculated. Adherence data will be available to the patient, caring CF physicians and coach in the IG, but not in the CG. At the end of the assessment phase, the IG is further stratified according to baseline adherence (adherence < 50% group and adherence ≥ 50% group). During the intervention phase, continuous digital monitoring of adherence to inhalation therapies and of lung function is performed in the IG. Participants of the IG can make use of video-conferencing with their caring CF physician up to three times per quarter. Participants of the IG with an adherence < 50% during the assessment phase additionally receive telephone coaching. In the case where mean adherence drops below 50% for at least four weeks in the first six months of the intervention phase in patients with initially good adherence (≥ 50%), these participants will receive a crisis talk followed by telephone coaching. In the last six months of the intervention phase, only monitoring and optional video-conferencing take place.

 = quarterly visit outpatient clinic,

 = intensive telephone coaching,

telephone coaching,

crisis phone call, t_0_ = inclusion into study, t_1_ = start assessment of adherence, t_2_ = start study intervention, t_3_ = six months of study intervention, t_4_ = 12 months of study intervention, t_5_ = end of study intervention

**Table 1 Tab1:** Overview of applied survey instruments and collected data for both the intervention and control group

Survey instrument/collected data	t0	t1	t2	t3	t4	t5
Anthropometric data	IG/CG		IG/CG	IG/CG	IG/CG	IG/CG
Sociodemographic data	IG/CG		IG/CG	IG/CG	IG/CG	IG/CG
Clinical history	IG/CG		IG/CG	IG/CG	IG/CG	IG/CG
Clinical findings	IG/CG		IG/CG	IG/CG	IG/CG	IG/CG
Lung function test	IG/CG		IG/CG	IG/CG	IG/CG	IG/CG
Therapy plan	IG/CG		IG/CG	IG/CG	IG/CG	IG/CG
Pulmonary exacerbations since last study visit	IG/CG		IG/CG	IG/CG	IG/CG	IG/CG
Time period until first pulmonary exacerbation since beginning of study intervention				IG/CG	IG/CG	IG/CG
Time between pulmonary exacerbations since last study visit	IG/CG		IG/CG	IG/CG	IG/CG	IG/CG
CF-associated hospital admissions since last study visit	IG/CG		IG/CG	IG/CG	IG/CG	IG/CG
Days absent from work or school since last study visit				IG/CG	IG/CG	IG/CG
CF-associated medical treatment and care since last study visit				IG/CG	IG/CG	IG/CG
Telemonitoring (App)						
Continuous monitoring of adherence to inhalation therapy		IG/CG	IG/CG	IG/CG	IG/CG	IG/CG
		continuously				
Weekly lung function measured by home spirometry^a^			IC	IC	IC	IC
			at least 1x/week			
Patient questionnaire						
Quality of life: EQ-5D-5L /. EQ-5D-Y-5L	IG/CG		IG/CG	IG/CG	IG/CG	IG/CG
Quality of life: CFQ-R	IG/CG		IG/CG	IG/CG	IG/CG	IG/CG
Beck Depression Inventar	IG/CG		IG/CG	IG/CG	IG/CG	IG/CG
Expectations and their fulfilment regarding the new form of care	IG/ relatives					IG/ relatives
Telephone interview						
acceptance, satisfaction, potential for optimization, barriers and implementation into standard care						IG/physician/ relatives

IG = intervention group, CG = control group, t_0_ = inclusion into study, t_1_ = start assessment of adherence, t_2_ = start study intervention, t_3_ = six months of study intervention, t_4_ = 12 months of study intervention, t_5_ = end of study intervention

^a^Lung function is measured at least weekly by home spirometry

The IG obtains a telemedicine capable nebulizer (eFlow rapid + nebulizer system consisting of an eTrack Controller with eFlow rapid nebulizer handset, PARI Pharma GmbH, Germany), home spirometry (mySpiroSense, PARI GmbH, Germany) and a CF therapy management app (PARI Connect App, PARI Pharma GmbH, Germany) to support self-management, provide adherence monitoring and transfer lung function values. The inhalation device can be used with all standard nebulized therapeutic agents. Data on date, duration, and inhaled agent will be collected and automatically transferred to a web cloud-based telemedicine data server. The CG also receives a telemedicine capable nebulizer (eTrack Controller with eFlow rapid nebulizer, PARI Pharma Ltd, Germany, and 2net Hub, Philips, North America). Data on adherence will be automatically tracked for final evaluation without any data access for participants or caring CF physicians in this group.

The adherence assessment phase follows the preparation phase. Over a minimum of four weeks, adherence to inhalation therapy will be tracked for both groups to obtain a baseline value for adherence before the intervention phase. Adherence is calculated by the ratio of the number of logged nebulization with a duration of more than one minute and the number of prescribed inhalation therapies. Adherence data will be available to the patient, caring CF physicians and coach in the IG, but not in the CG. The IG is further stratified according to baseline adherence (adherence < 50% subgroup and adherence ≥ 50% subgroup).

During the intervention phase of 18 months duration, continuous digital monitoring of adherence to inhalation therapies and of lung function is performed in the IG. Performed inhalation therapies are compared to individual therapy plans and adherence is calculated and displayed both to the patient and caring CF physician. Lung function measurements via home spirometry are performed at least once per week, ideally at the same time of day and following bronchodilator therapy (if applicable). A progressive graph is generated from lung function data and provided to the CF physician. Additionally, the IG participants can make use of video-conferencing with their caring CF physician up to three times per quarter. While the patient can request video-conferencing, the CF physician will also recommend this option if the patient's FEV1 decreases by > 5% compared to the mean of the previous two measurements.

All the IG participants will receive continuous monitoring and optional video-conferencing, and participants with an adherence < 50% during the assessment phase will receive telephone coaching. Psychologist from Thieme TeleCare Ltd. will carry out telephone coaching. It is based on a necessity-concern-framework and consists of two phases: change talk and commitment talk. The coaching's primary goals include supporting the patient with disease management, creating awareness of possible issues with therapy adherence, increasing motivation for adherence, strengthening the perception of risks of non-adherence, and involving parents, partners, or close relatives (23). This coaching will take place twice per month for the first six months and once per month in the following six months. In the case where mean adherence drops below 50% for at least four weeks in the first six months of the intervention phase in patients with initially good adherence (≥ 50%), these participants will receive a crisis talk and intensive telephone coaching (twice/months) for the following six months. This intervention will be followed by a phase of reduced telephone coaching, whereby the number of months with reduced coaching depends on the time left in the intervention phase. In the last six months of the intervention phase, only monitoring and optional video-conferencing occur to assess the effect of the coaching. In the CG, continuous digital monitoring of adherence to inhalation therapies is performed as well, but calculated adherence is neither displayed to the patient nor to the CF physician.

